### Outcomes

Efficacy of the interventions will be determined by comparing change scores (baseline to post treatment) on a variety of standardized outcome measures taken at baseline, post-treatment and 8 weeks post-intervention. The primary outcome measure is comfortable gait speed as measured by the five-metre walk test [54]. Following stroke, gait speed is frequently reduced compared to age matched normals [5,55,56]. Gait speed has been shown to be reliable (r = 0.94)[57], responsive to change (SRM = 1.22; effect size = 0.83) [54], and significantly related to independent community ambulation [11].

Secondary outcome assessment will include measures of maximal gait speed, walking endurance (Six Minute Walk Test), dynamic balance (Functional Balance Test) [58], balance and walking related self-efficacy (Activities- specific Balance Confidence Scale) [59], walking function (modified Functional Ambulation Categories) [60], walking participation (5-day daily step activity - StepWatch 3 step activity monitor) [61,62], community reintegration (Life Space Questionnaire) [63,64], health related quality of life (Stroke Impact Scale 3.0) [65], goal attainment (Patient Specific Functional Scale) [66] and mean number of trainers per training session.

In addition, the baseline assessment will include the collection of demographic information, assessment of cognitive function (Mini Mental Status Exam) [36], presence of depression (Geriatric Depression Scale -15) [67], and the Chedoke-McMaster Stroke Assessment Leg and Foot stages of motor recovery [68]. At follow-up, information will be collected regarding participation in physiotherapy and any change in health status. This information will be used to describe the groups and interpret the results of the interventions.

Training and assessor therapists will record any of the following adverse events that occur during or between sessions: 1) falls (unintentionally landing on the ground), 2) any injury during session, 3) myocardial infarction (confirmed by physician and/or health records), 4) new stroke or transient ischemic attack (confirmed by physician and/or health records), 5) hospitalization for any cause, 6) death of any cause.

Physiotherapists trained to perform the standardized outcome measures will measure outcomes. Assessors will be blinded to the participant's intervention assignment and study hypotheses, limiting the potential for expectation bias. Participants will be instructed not to reveal their group assignment to the assessor.

Outcome assessment domains, tools and timing are summarized in Table 2.

**Table 2 T2:** Outcome domains, measures and timing of assessments

*ICF*	*Domain*	*Instrument*	*Screening/Baseline*	*Post -Intervention*	*Follow-up*
Personal and Environmental Factors	Stroke details	Interview, health record review	X		
	Comorbidities		X		
	Living situation		X		
	Gait aid		X	X	X
	Physiotherapy		X	X	X
	Fall history		X	X	X
	Adverse events		X	X	X
Body Structures/Function	Motor recovery	Chedoke-McMaster Stroke Assessment	X		
	Cognition	Mini Mental Status Examination	X		
	Depression	Geriatric Depression Scale Short form-15	X		
Activity	Walking speed	5 metre walk test	X	X	X
	Walking endurance	Six Minute Walk Test	X	X	X
	Dynamic balance	Functional Balance Test	X	X	X
	Balance self-efficacy	Activities-specific Balance Confidence Scale	X	X	X
	Goal attainment	Patient Specific Functional Scale	X	X	X
Participation	Walking independence	Modified Functional Ambulation Categories	X	X	X
	Daily walking activity	Step Watch 3.0 step activity monitor	X	X	X
	Mobility participation	Life Space Questionnaire	X	X	X
	Health related quality of life	Stroke Impact Scale 3.0	X	X	X

ICF = International Classification of Function domains

### Sample size

Seventy participants will be recruited. The sample size has been calculated to reliably detect a 0.14 m/s between-group difference in gait speed change (assuming a standard deviation of 0.19 m/s) with 80% power at a 2-tail significance level of 0.05. Using self-selected gait speed as the primary outcome, this sample size has been estimated based on a range of change scores and standard deviation values reported in the literature. Reported differences in change scores between experimental and control interventions range from 0.9 m/s to 0.14 m/s and standard deviation in change scores range from 0.14 to 0.19 m/s [19,33,34,69,70]. Using a conservative estimate of standard deviation of change score of 0.19 and a difference between group change scores of 0.14 m/s, the minimal number of participants required for each treatment group is 29 participants. Dropout rates in previous studies have ranged from 7 to 20% [19,33]. Allowing for a 17% loss to follow up rate, the study will need to recruit approximately 35 participants into each group for a total of 70.

### Statistical Analysis

The trial results will be reported in accordance with the CONSORT criteria [http://www.consort-statement.org]. The flow of patients in the trial will be summarized using a flow-diagram. The baseline characteristics and outcomes scores of the patients will be analyzed using descriptive statistics reported by group as mean (standard deviation [SD]) or median (first quartile [Q1], third quartile [Q3]) for continuous variables depending on the distribution and count (percent) for categorical variables. Intention to treat analysis technique will be used for the primary analysis [71]. Missing data will be handled through multiple imputation technique [72]. All statistical tests will be performed using two-sided tests at the 0.05 level of significance. The Tukey's HSD method will be used to adjust the level of significance for testing for secondary outcomes. For all models, the results will be expressed as estimate of mean difference (or odds ratios for binary outcomes), standard errors, corresponding two-sided 95% confidence intervals and associated p-values. P-values will be reported to three decimal places with values less than 0.001 reported as < 0.001. Adjusted analyses will be performed using regression techniques to investigate the residual impact of key baseline characteristics on the outcomes (i.e. age, time since stroke onset, comfortable gait speed, and training site). Goodness-of-fit will be assessed by examining the residuals for model assumptions and chi-squared test of goodness-of-fit. All analyses will be performed using SPSS version 16.0 for Windows or SAS 9.2 (Cary, NC).

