### Randomization

Participants will be randomly allocated to the two active intervention groups using a fixed allocation ratio of 1:1. Consistent with previous studies in this area [19,33], we anticipate the response to both training programs to be associated with pre-treatment walking ability and participants will be stratified by baseline comfortable gait speed (slow < 0.5 m/s and fast ≥ 0.5 m/) to minimize group imbalances on this variable [37]. In order to maintain recruitment balance between groups throughout the trial, a permuted block randomization process will be used within each strata using block sizes of at least 2 with all blocks divisible by 2 [38]. The randomization creation process (including block sizes) and resulting schedule will be set, held and managed by a central randomization service (Biostatistics Unit at St. Joseph's Healthcare Hamilton). Group assignment will be communicated by email to the research coordinator on a single participant basis after screening, written informed consent, and baseline assessments have been completed.

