#### Secondary Analysis

Mixed design analysis of variance will be used to compare the two groups' baseline, post-intervention and follow-up scores on all other secondary measures. The two factors will be time and group. Descriptive statistics (i.e. means, or frequencies) will be used to present data related to adverse and serious adverse events by groups. Any apparently significant differences between groups will be analysed for significance using chi square statistics. In an effort to describe the two interventions, the mean number of steps taken per session will be counted in a convenient sub-sample of participants using the step activity monitors. Independent samples t-test statistic will be used to compare the mean number of steps taken per session by the two groups during treatment sessions.

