**2) Secondary (T2, T3)**			
Secondary outcomes			
a) Fast walking speed	MLWP > BWSTT	Fast Gait Speed (c)	ANCOVA
b) Walking endurance	MLWP > BWSTT	Six minute walk test(c)	ANCOVA
c) Balance and walking related self-efficacy	MLWP > BWSTT	Activities-specific Balance Confidence Scale (c)	ANCOVA
d) Dynamic balance	MLWP > BWSTT	Functional Balance Test(c)	ANCOVA
e) Mobility participation	MLWP > BWSTT	Life Space Questionnaire (c)	ANCOVA
f) Health-related quality of life	MLWP > BWSTT	Stroke Impact Scale 3.0 (c)	ANCOVA
g) Goal attainment	MLWP > BWSTT	Patient Specific Function Scale(c)	ANCOVA
h) Walking participation	MLWP < BWSTT	Mean daily step activity	ANCOVA
i) Training staff requirement	MLWP < BWSTT	Total number of trainers/number of training sessions (c)	T-test
j) Meaningful change in gait speed of ≥ 0.14 m/s	MLWP > BWSTT	Comfortable gait speed change score T2-T1 ≥ 0.14 m/s)(b)	Chi-square test
Adverse events (count)			
a) Falls during session		Therapist report (b)	Chi-square test
b) Injury during session		Therapist report (b)	Chi-square test
c) Falls between session		Patient report (b)	Chi-square test
d) Myocardial Infarction		Patient report/health record (b)	Chi-square test
e) New stroke		Patient report/health record (b)	Chi-square test
f) Hospitalization		Patient report/health record (b)	Chi-square test
g) Death (all causes)		Health record/Physician (b)	Chi-square test

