**3) Sensitivity Analysis**			
a) All outcomes analysed simultaneously to account for correlation among them		Primary and secondary outcomes	MANOVA
b) Serial correlation of all outcomes at baseline, T2, T3		Primary and secondary outcomes	GEE
c) Completers (≥ 12 sessions)	MLWP > BWSTT	Comfortable Gait speed	ANCOVA

IMPORTANT REMARKS:

The GEE^2 ^is a technique that allows to specify the correlation structure between patients within a hospital and this approach produces unbiased estimates under the assumption that missing observations will be missing at random. An amended approach of weighted GEE will be employed if missingness is found not to be at random^3^.

In all analyses results will be expressed as coefficient, standard errors, corresponding 95% and associated p-values. Goodness-of-fit will be assessed by examining the residuals for model assumptions and chi-squared test of goodness-of-fit

Tukey's HSD method will be used to adjust the overall level of significance for multiple secondary outcomes

^2^Hardin JW. *Generalized Estimating Equations*. New York: Chapman and Hall/CRC, 2001

^3 ^Diggle PJ, Liang K-Y, Zeger S. *Analysis of Longitudinal Data*. Oxford: Oxford Science Publications, 1994.

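### Tukey's HSD is named to adjust across the secondary outcomes, but it works within one outcome and gives no designed control over the family of outcomes

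*Protocol article*

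**What the plan says.** The multiplicity rule appears twice. Under Statistical Analysis: "The Tukey's HSD method will be used to adjust the level of significance for testing for secondary outcomes". In the remarks below Table 3, where the purpose is explicit: "Tukey's HSD method will be used to adjust the overall level of significance for multiple secondary outcomes". The general rule is "All statistical tests will be performed using two-sided tests at the 0.05 level of significance".

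The trial has two arms: "Participants will be randomly allocated to the two active intervention groups using a fixed allocation ratio of 1:1".

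Table 3, under "2) Secondary (T2, T3"), lists ten secondary outcomes, from "a) Fast walking speed" to "j) Meaningful change in gait speed of ≥ 0.14 m/s". Rows a to h are assigned ANCOVA, row i (trainers per session) a t-test and row j a chi-square test. Each is a comparison of MLWP with BWSTT.

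The Secondary Analysis section describes a different model for the secondary measures, a mixed-design analysis of variance over baseline, post-intervention and follow-up: "The two factors will be time and group".

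MANOVA over all outcomes is listed only among the sensitivity analyses. No hierarchy, gatekeeping or other adjustment across outcomes is stated.

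**The concern.** The protocol undertakes to control error over several secondary outcomes and names a procedure that does something else. HSD protects the set of pairwise differences among group means on one response variable. It takes no account of how many response variables are tested. With two arms, each outcome offers one between-arm difference, so HSD has nothing to adjust.

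What is at stake is the reading of the secondary results. A report that follows this plan could say that secondary p-values were adjusted for multiplicity when no adjustment across outcomes had taken place. That is more misleading than openly unadjusted testing, because readers would discount the results less than they should.

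**Working it through.** **The plan's own figures.** The documents state no adjusted significance level and no family-wise error rate, so there is none to reproduce. The sample size, used here only for degrees of freedom, does reproduce. With a difference of 0.14, SD 0.19, two-sided 0.05 and 80% power, n per arm = 2 × (1.960 + 0.842)² × (0.19/0.14)² ≈ 28.9, so 29. Then 29/0.83 = 34.9, so 35 per arm and 70 in total.

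**Step 1: HSD with two groups.** HSD declares a difference when |t| exceeds q(0.95; k, df)/√2, where q is the studentized-range quantile and k the number of means.

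- 29 per arm, df = 58 − 2 = 56, k = 2: q = 2.8330, and 2.8330/√2 = 2.00324. The ordinary t critical value is 2.00324.
- 35 per arm, df = 70 − 2 = 68, k = 2: 2.8220/√2 = 1.99547. The t critical value is 1.99547.
- One further degree of freedom for the speed stratum in the ANCOVA (df 55 or 67) leaves the identity intact: 2.00404 and 1.99601 on both sides.

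The level for each outcome after HSD is therefore 0.0500.

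**Step 2: HSD inside the mixed ANOVA.** Taking 56 df as an approximation:

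- three time-point means, k = 3: critical |t| = 2.4076, per-comparison level about 0.019
- six group-by-time cells, k = 6: critical |t| = 2.9507, per-comparison level about 0.0046

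Both levels depend on the number of means within one outcome. Neither changes with the number of outcomes. The three-mean version compares time points, not arms.

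**Step 3: row j.** This is a binary outcome tested by chi-square. HSD compares means and has no standard form for it.

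**Step 4: size of the uncontrolled error when each test is at 0.05.** For m independent tests, the chance of at least one false positive is 1 − 0.95^m. For m tests with common correlation ρ, it is 1 − ∫ φ(z) [Φ((c − √ρ z)/√(1−ρ)) − Φ((−c − √ρ z)/√(1−ρ))]^m dz, with c = 1.960. The correlation is an assumption: the Sensitivity Analyses section expects it to be high but gives no figure.

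| Family | ρ = 0 | ρ = 0.5 | ρ = 0.7 | ρ = 0.9 |
|---|---|---|---|---|
| Rows a–h, one time point (m = 8) | 33.7% | 25.0% | 19.1% | 11.9% |
| Rows a–h, T2 and T3 (m = 16) | 56.0% | 37.4% | 26.4% | 14.6% |

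Simulation with 100,000 draws agrees with every entry to within 0.3 percentage points.

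**Step 5: direction.** The tests are two-sided, so under the null each false positive is equally likely to favour either arm. For 16 independent tests, the chance of at least one that favours MLWP is 1 − 0.975^16 = 33%, not 56%.

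**The case against.** The strongest objection is that the Secondary Analysis section specifies a mixed ANOVA, where HSD is a familiar follow-up and does tighten comparisons. If it were applied to all six group-by-time cells, each between-arm contrast would face a level of about 0.0046. The 16 contrasts would then carry a chance of a false positive of about 7% if independent (1 − (1 − 0.0046)^16), 5% at correlation 0.5 and 4% at 0.7. So a reader who infers that every secondary test would be run at an unadjusted 0.05 goes too far: that holds for the ANCOVA of Table 3, not necessarily for the mixed model. But this protection is a by-product of the number of cells and would be the same for two outcomes or twenty. The Table 3 remarks tie HSD to multiple outcomes, and Table 3 assigns ANCOVA to rows a to h.

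Two other strong readings are not supported.

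- **A 60% error rate.** Rows a to h at two times plus rows i and j make 18 tests, and 1 − 0.95^18 = 60%. This assumes independence, which the protocol argues against. It also counts row i, where Table 1 sets different staffing for the two arms by design, so its null is not in play.
- **A likely false claim for the experimental programme.** Not all hypotheses favour MLWP: row h is written as MLWP < BWSTT for daily step activity. Two-sided false positives can also fall on either side.

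It is also fair to say that there is a single primary outcome at one time point, that estimates and confidence intervals will accompany all p-values, and that a global MANOVA is planned. The MANOVA is not stated to gate the individual tests, so it does not supply the missing control.

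A separate SAP might refine the method. The procedure is nevertheless already fixed in the article, twice, and is wrong for its stated purpose.

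**Conclusion.** The point holds, and it should be fixed. The named method cannot deliver the stated control across secondary outcomes under either of the two models in the protocol. Under Table 3's ANCOVA it is exactly the unadjusted test at 0.05. Under the mixed ANOVA any tightening is within an outcome only.

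At an unadjusted 0.05, the risk of at least one false positive over rows a to h runs from about 12% to 34% at one time point and from about 15% to 56% over T2 and T3, as the common correlation goes from 0.9 to 0. Given the correlation the protocol expects, the lower part of each range is the more realistic, still two to three times the nominal 5% at correlation 0.9. These figures assume that all the nulls are true, a common correlation and normally distributed test statistics.

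The defect is confined to the secondary outcomes. The alpha, power and sample size for the primary outcome are untouched.

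**What to change.** Replace the Tukey sentence under Statistical Analysis and in the Table 3 remarks with a procedure valid across outcomes. Holm is suitable: it needs only p-values and assumes nothing about correlation. The replacement should settle four things:

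1. **Source of the p-values.** Use the between-group comparison for rows a to h from one stated model, reconciling Table 3's ANCOVA with the mixed ANOVA in the Secondary Analysis section.
2. **The family.** Either one family over T2 and T3 (first Holm step 0.05/16 = 0.003125), or one family per time point (first step 0.05/8 = 0.00625). The second option needs a statement that control is within time point only, since two families at 0.05 allow up to about 10% overall.
3. **Row i.** Leave it out, as a process measure.
4. **Row j.** Say whether it is included, since it dichotomises change in the primary outcome. If it is, the family size and first step change accordingly.

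An equally valid alternative is to delete the adjustment claim in both places and label the secondary p-values unadjusted and exploratory.

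The cost is a few sentences. Under Holm the adjusted secondary p-values become larger, so fewer secondary differences will reach significance. The change should be made before unblinded analysis.

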#### Primary Analysis

The post-intervention (T2) self-selected overground walking speed for the MLWP and BWSTT groups will be compared using analysis of covariance. The two factors will be intervention group (intervention or control) and baseline speed stratum (i.e. slow or fast).

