**Methods/Design:**

A parallel, randomized controlled trial with stratification by baseline gait speed will be conducted. Allocation will be controlled by a central randomization service and participants will be allocated to the two active intervention groups (1:1) using a permuted block randomization process. Seventy participants will be assigned to one of two 15-session training programs. In MLWP, one physiotherapist will supervise practice of various overground walking tasks. Instructions, feedback, and guidance will be provided in a manner that facilitates self-evaluation and problem solving. In BWSTT, training will emphasize repetition of the normal gait cycle while supported over a treadmill, assisted by up to three physiotherapists. Outcomes will be assessed by a blinded assessor at baseline, post-intervention and at 2-month follow-up. The primary outcome will be post-intervention comfortable gait speed. Secondary outcomes include fast gait speed, walking endurance, balance self-efficacy, participation in community mobility, health-related quality of life, and goal attainment. Groups will be compared using analysis of covariance with baseline gait speed strata as the single covariate. Intention-to-treat analysis will be used.

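### The primary ANCOVA adjusts only for the slow/fast stratum, although baseline speed is measured, and the 80% power was computed for a different analysis (change scores)

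*Protocol article*

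**What the plan says.** The Primary Analysis section of the protocol article analyses T2 comfortable speed by analysis of covariance and names its terms: "The two factors will be intervention group (intervention or control) and baseline speed stratum (i.e. slow or fast"). The Abstract (Methods/Design) leaves no room for a further covariate: "Groups will be compared using analysis of covariance with baseline gait speed strata as the single covariate". The primary row of Table 3 gives T2 comfortable gait speed and ANCOVA without naming covariates, which is compatible.

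The Sample size section is written for another quantity. It aims to "reliably detect a 0.14 m/s between-group difference in gait speed change (assuming a standard deviation of 0.19 m/s) with 80% power", and repeats the basis: "Using a conservative estimate of standard deviation of change score of 0.19 and a difference between group change scores of 0.14 m/s". The Outcomes section also speaks of change: "Efficacy of the interventions will be determined by comparing change scores (baseline to post treatment").

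Comfortable speed is measured at baseline by the five-metre walk test (Outcomes, Table 2). As an adjustment variable it appears only among the additional adjusted regressions in the Statistical Analysis section.

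**The concern.** A change score subtracts each participant's own baseline value. A model with a two-level stratum removes only the difference between the slow and fast group means; the baseline spread within each stratum stays in the error term. The SD of change is therefore not the error SD of the planned test, and a power figure based on it does not carry over.

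Two things are at stake. The decisive test may be less precise than data already collected would allow, in a trial of 70 people. And the stated 80% power describes an analysis that is not the primary one. In addition, the Outcomes sentence on change scores and the Primary Analysis section describe the efficacy comparison differently.

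**Working it through.** **Inputs from the Sample size section.** Difference 0.14 m/s, SD of change 0.19 m/s, two-sided 0.05, 80% power, 29 per group, 17% loss. The stratum cut is 0.5 m/s (Design Outline).

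**Step 1: the plan's own figure.** n = 2(1.960 + 0.842)² × 0.19² / 0.14² = 28.9, so 29 per group. 29 / 0.83 = 34.9, so 35 per group and 70 in total. Power at 29 per group is 80% by the normal approximation and 79% by the noncentral t. The arithmetic is right, for a two-sample comparison of change.

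**Step 2: residual SD of the two candidate models.** The document gives neither the SD of speed nor the baseline-to-T2 correlation. I assume the same SD, s, at both times and hold the SD of change at 0.19:

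- Correlation: ρ = 1 − 0.19² / (2s²).
- Stratum only: residual SD = s√(1 − kρ²), where k is the share of baseline variance that the split captures.
- Continuous baseline: residual SD = s√(1 − ρ²) = 0.19√((1 + ρ)/2).

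For a normal baseline cut at its median, k = 2/π = 0.637. For a baseline uniform on 0.1 to 1.0 m/s cut at 0.5, k = (4/9)(5/9)(0.45²) / (0.9²/12) = 0.74.

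**Step 3: power at 29 per group, true difference 0.14** (noncentral t; noncentrality 0.14 / (residual SD × √(2/29)), 55 df).

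| s | ρ | Residual SD, stratum only (k = 0.637 / 0.74) | Residual SD, continuous | Power, stratum only | Power, continuous |
|---|---|---|---|---|---|
| 0.20 | 0.55 | 0.180 / 0.176 | 0.167 | 83% / 84% | 88% |
| 0.25 | 0.71 | 0.206 / 0.198 | 0.176 | 72% / 75% | 85% |
| 0.26 | 0.73 | 0.211 / 0.202 | 0.177 | 70% / 74% | 84% |
| 0.30 | 0.80 | 0.231 / 0.218 | 0.180 | 62% / 67% | 83% |

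With k = 0.75 (uniform baseline cut at its midpoint) the 0.25 row gives 76%. Simulation with stratified 1:1 allocation, normal baseline and median cut gave 86%, 72%, 62% and 43% for stratum only at ρ = 0.5, 0.7, 0.8 and 0.9. For continuous baseline it gave 89%, 85%, 83% and 81%. The change-score test stayed at 79-80%.

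**Step 4: break-even.** The stratum-only residual SD equals 0.19 when kρ² − 2ρ + 1 = 0, so ρ = (1 − √(1 − k))/k. For k = 0.637 this is 0.62 (s about 0.22). Over cuts that put 20% to 50% of participants in one stratum, and for a uniform baseline, it runs from 0.58 to 0.67. Above it, the planned test has less power than stated; below it, more.

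**Step 5: the continuous model against 0.19.** Since (1 + ρ)/2 ≤ 1, its residual SD cannot exceed 0.19 when the two SDs are equal.

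**The case against.** The strongest defence is that the planned model is sound. It adjusts for the randomisation stratification factor, is unbiased under randomisation and keeps its type I error. That stands: the cost is precision, not validity.

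Second, a reader might infer that the trial is underpowered. The documents do not show this. At s = 0.20 the planned test exceeds 80%, and the deciding correlation is not given. The Outcomes section quotes a standardised response mean of 1.22 and an effect size of 0.83. On the usual definitions these imply an SD of change of 0.83/1.22 = 0.68 of the baseline SD, hence s = 0.19/0.68 = 0.28 and ρ = 1 − 0.68²/2 = 0.77. But those figures come from a cited sample, the definitions are not stated, and this trial's entry limit may narrow the spread.

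Third, the s = 0.30 row is extreme. Entry requires a speed below 1.0 m/s unless a walking aid is typically used, and a uniform spread over 0.1 to 1.0 has an SD of only 0.9/√12 = 0.26. The plan also calls 0.19 conservative, the top of a 0.14 to 0.19 range. With an SD of change of 0.165, s = 0.26 and k = 0.74, the planned test has about 79-80% power. Both points temper the size of the loss, but the gap to the continuous model remains.

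Fourth, baseline speed is not ignored altogether: the adjusted regressions name it, and the GEE sensitivity analysis uses the baseline measurements. Readers will see such estimates, but the primary test stays as specified.

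Finally, a reader might count three competing specifications (change score, post score, stratum-only ANCOVA). There are two, because the ANCOVA is the analysis of the post score. The outlier is the general opening sentence of Outcomes, and the Primary Analysis section governs.

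**Conclusion.** The point holds as a mismatch between the power calculation and the primary model, together with an avoidable loss of precision. The 29, 35 and 70 are correct for a change-score comparison and do not establish the power of the planned test. Under equal SDs, a true difference of 0.14 m/s and 29 evaluable per group, the planned test has about 83-84% power at s = 0.20 and about 70-76% at s = 0.25-0.26. The continuous-baseline model has about 88% and 84-85%. At s = 0.30 (62-67% against 83%) the loss is larger, but that case is unlikely given the entry limit. The continuous model did better in every case computed. Neither invalidity of the planned test nor a definite shortfall below 80% follows from the document.

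**What to change.** Make the primary model an ANCOVA of T2 comfortable gait speed on treatment, continuous baseline comfortable gait speed and the randomisation stratum. Align the Abstract (Methods/Design), Outcomes, Primary Analysis and Table 3 to that one model.

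In Sample size, keep 0.19 m/s as the SD of change, which is what the literature values are. It should not be relabelled as the model's residual SD. Add that, under equal SDs before and after treatment, it is a conservative upper bound on that residual SD (0.167 to 0.180 in the table above), so 29 per group keeps about 80% power or more.

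The cost is one degree of freedom and a change of wording. The number recruited does not change and no new data are needed. If the stratum-only model is kept instead, its power should be restated from an assumed within-stratum SD of T2 speed.
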